#### Secondary Outcomes

The secondary outcomes are as follows:

Neck-shaft angle: defined as the angle between the longitudinal axis of the femoral shaft and the axis of the femoral neck, as measured on postoperative radiographsGuide wire placement quality (TCS groups): classified according to guide wire arrangement as 3 parallel, 2 parallel, or nonparallel, as determined from intraoperative imagingOperative time: measured from the initial skin incision to complete wound closure, as documented in intraoperative recordsIntraoperative blood loss: quantified as the total blood volume collected by the suction apparatus during the operationFracture healing status: assessed using anteroposterior and lateral hip radiographs at 1, 3, 6, and 12 months and computed tomography scans at 1 and 3 months by evaluating implant stability, disappearance of the fracture line, and absence of displacement at the fracture siteZarit Caregiver Burden Score: evaluated using an established questionnaire to assess the perceived level of caregiving burden experienced by caregivers of patients after a fractureHarris Hip Score: assessed using the Harris scoring system during outpatient visits at 1, 3, 6, and 12 months postoperatively to evaluate hip joint function36-Item Short Form Health Survey Score: assessed using the 36-Item Short Form Health Survey at 1, 3, 6, and 12 months postoperatively to reflect the patient’s overall physical and mental health trajectory

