### Description of the Novel Device

The navigation system primarily consists of a surgical planning workstation (laptop computer), a surgical navigation console, and a navigation instrument table. The entire setup has a minimal footprint and features user-friendly operation. The main procedural workflow proceeds as follows. First, anteroposterior and lateral views of the target lesion area are acquired, ensuring that all marker spheres of the image registration device and the target lesion area are included. Next, after determining whether distortion correction is needed based on the intraoperative use of a C-arm (equipped with a flat-panel detector or image intensifier), registration verification and trajectory planning for TCS are performed on the workstation system. This system enables simultaneous planning of all TCS, eliminating the need for repeated adjustments to optimize their spatial relationship and thereby reducing surgical time. Finally, guide wires are implanted along the planned trajectories, and subsequently, depth measurement and TCS insertion are completed (Figure 2).

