### Randomization and Blinding

This is a single-blind trial in which patients and outcome assessors will be blinded to treatment allocation, while operating surgeons cannot be blinded because of the distinct intraoperative workflows associated with the navigation system and the freehand technique. Patients will remain blinded to their group assignment throughout the surgical procedure and the entire 12-month follow-up period, with the specific technique disclosed only after completion of all outcome assessments unless early unblinding is required for safety reasons. Radiographic assessors and functional outcome assessors will be blinded to group allocation, as all imaging studies and clinical assessments will be coded with unique participant identifiers and conducted without access to treatment assignment records. The primary statistical analyst will remain blinded until the final database is locked and all predefined analyses are completed, with group codes revealed only after the statistical analysis plan has been fully executed. Emergency unblinding may be performed by the principal investigator in the event of a serious adverse event for which knowledge of the intervention is essential for patient management, and any such event will be documented and reported.

Randomization will be performed by the coordinating center using a centralized computer-generated system with permuted blocks of 4 to ensure balanced allocation across treatment groups. Assignment details will be distributed to all participating sites via sequentially numbered, sealed opaque envelopes. All surgical procedures will be performed in accordance with the assigned randomization.

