#### Intervention Group: NS+TCS Fixation

Following successful anesthesia, the patient is positioned supine on a traction table. Satisfactory reduction of the fracture fragments is achieved under G-arm fluoroscopic guidance. The operative field is routinely prepared and draped in a sterile fashion.

Two guide pins are inserted, one at the anterior superior iliac spine and another at the lateral femoral condyle, to serve as anchoring points. A navigation reference array is then mounted. The exposed ends of the guide pins are trimmed to an appropriate length to avoid interference with subsequent fluoroscopic imaging. Image registration markers are positioned anteriorly and laterally to the hip joint. Standard anteroposterior and lateral hip radiographs are acquired and uploaded to the navigation system workstation for preoperative trajectory planning for TCS placement. An inverted triangular configuration is selected for dispersed screw placement. After calibration of the navigated drill sleeve, the planned trajectories are used to percutaneously insert 3 guide wires sequentially into the femoral neck and head through small skin incisions. Subsequently, TCS are inserted over the guide wires. Fluoroscopic confirmation is obtained to verify satisfactory screw length and position.

Upon confirmation of adequate fixation, the reference guide pins at the anterior superior iliac spine and lateral femoral condyle are removed. The surgical incisions are irrigated and closed in layers (Figure 3).

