**Secondary outcomes**					
	Neck-shaft angle	Angle between the femoral shaft axis and the femoral neck axis		Intraoperative period	
	Guide wire placement accuracy	Classification of guide wire arrangement as 3 parallel, 2 parallel, or nonparallel		Intraoperative period	
	Surgical duration	Time from skin incision to wound closure		Intraoperative period	
	Intraoperative blood loss	Total blood loss collected through suction		Intraoperative period	
	Fracture healing status	Fracture healing assessed by implant stability, disappearance of the fracture line, and absence of displacement		1, 3, 6, and 12 months	
	Zarit Caregiver Burden Score	Assessment of caregiver burden		1, 3, 6, and 12 months	
	Harris Hip Score	Assessment of hip function recovery		1, 3, 6, and 12 months	
	36-Item Short Form Health Survey Score	Assessment of health-related quality of life		1, 3, 6, and 12 months	

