## Results

This multicenter, prospective, randomized controlled trial was initiated in June 2024. Enrollment is scheduled to be completed by October 2026, with a target sample size of 300 participants. The final 12-month follow-up is expected to be completed by October 2027. Data cleaning and database locking will be performed within 3 months thereafter, followed by analyses of the primary and secondary outcomes.

The feasibility of implementing this protocol in future larger-scale studies will be evaluated using the following metrics: (1) navigation system performance will be assessed for each procedure in the intervention group, including trajectory planning accuracy, reference array stability, first-pass guide wire success rate, and the incidence of technical failures or device deficiencies; (2) retention rates will be assessed through completion of scheduled follow-up visits, imaging protocols, and patient-reported outcome measures; and (3) the volume of intraoperative data collected—including fluoroscopy frequency, operative time, blood loss, neck-shaft angle, and guide wire placement quality—will be quantified to inform data management strategies in future investigations.

Any deviations from the approved protocol will be documented and categorized as major or minor. All deviations will be reported to the coordinating center’s institutional review board and to the ethics committees of participating sites. Moreover, the clinical value of incorporating the navigation system will be determined by comparing the primary and secondary outcomes between the 2 treatment groups after trial completion. The results of this trial will provide evidence on the viability of navigation-assisted surgery using a fluoroscopy-based, workflow-preserving system for FNF fixation.

Upon completion of the trial, the results will be submitted for publication in peer-reviewed orthopedic or surgical journals, regardless of the direction of the outcomes. The coordinating center will be responsible for drafting the primary manuscript. There are no intended restrictions on the publication of results. This trial protocol has been prospectively registered on ClinicalTrials.gov (NCT06713018), and any significant protocol amendments will be documented and publicly disclosed.

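### Guide wire arrangement, the only named between-arm placement outcome, is read from images taken while navigation-only pins are in place, and coding the images would not hide the arm if they show it

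*Protocol article*

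**What the plan says.** **The outcome.** Secondary Outcomes defines guide wire placement quality as "classified according to guide wire arrangement as 3 parallel, 2 parallel, or nonparallel, as determined from intraoperative" imaging. Table 1 lists the same item as "Guide wire placement accuracy", assessed in the intraoperative period.

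**The blinding.** Randomization and Blinding states: "Radiographic assessors and functional outcome assessors will be blinded to group allocation". The means given is "as all imaging studies and clinical assessments will be coded with unique participant identifiers and conducted without access to treatment assignment records". Surgeons are acknowledged to be unblinded.

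**The hardware.** Only the navigated arm carries extra hardware. Under Intervention Group: NS+TCS Fixation, "Two guide pins are inserted, one at the anterior superior iliac spine and another at the lateral femoral condyle, to serve as anchoring points". A reference array is mounted, and registration markers are placed in front of and beside the hip. The pin ends are "trimmed to an appropriate length to avoid interference with subsequent fluoroscopic imaging". The pins are removed only after fixation has been judged adequate. For the registration views, Description of the Novel Device asks for views "ensuring that all marker spheres of the image registration device and the target lesion area are included".

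**Other placement information.** Follow-Up Visits has postoperative radiographs and CT reviewed for the position of the fixation, but no listed outcome is built on that review. Neck-shaft angle is measured on postoperative radiographs and describes alignment, not wire or screw placement. First-pass guide wire success appears in the Results section among feasibility metrics, where "navigation system performance will be assessed for each procedure in the intervention group". It is not in the outcome list.

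**The concern.** A participant code masks a label, not the content of a picture. If a scored view shows a pin or part of the array, the assessor knows the arm whatever the code says. The image series could also give it away. Primary Outcome sorts the images into reduction, navigational positioning and implant placement, and the middle category should exist only for navigated cases. The planning means also differ widely (32.2 against 15.2 images).

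The likely direction of any bias is clear. The Discussion expects guide wire placement quality to favour navigation, and the Introduction says the research group co-developed the device. The Abstract names suboptimal operative accuracy as one of the limitations of freehand fixation that motivate the trial. Strengths and Limitations relies on blinded assessment to reduce detection bias. For this outcome the stated mechanism does not secure that, so a between-arm difference in wire arrangement could be questioned.

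**Working it through.** **Step 1: order of events in the navigated arm (Intervention Group: NS+TCS Fixation).**
1. Pins and array are mounted, and registration markers are positioned.
2. Registration views are taken and uploaded, and trajectories are planned.
3. Three guide wires are inserted, then screws over them.
4. Fluoroscopy confirms screw length and position.
5. Pins are removed.

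Wire arrangement can be seen only from step 3 on, so the pins are still in place in every image that could be scored. The marker-sphere requirement belongs to step 2 and does not describe the scored images. The control arm has no pins.

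**Step 2: blinding mechanism against image content.** Coding and withheld assignment records act on labels and files. The protocol states no cropping, masking or selection of views. The trimming of the pins is there for image clarity. Whether the pins (iliac spine and femoral condyle) fall inside a hip view is not stated.

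**Step 3: number of patients.** The protocol gives no figure for this outcome, so I take its planned group size after reproducing it. Inputs from Sample Size: means 32.2 and 15.2, SDs 5.2 and 3.7, margin 15.4, one-sided 0.025, power 0.8.
- Pooled SD = √[(5.2² + 3.7²)/2] = 4.513
- Difference beyond the margin = 32.2 − 15.2 − 15.4 = 1.6
- n = 2 × [4.513 × (1.960 + 0.842)/1.6]² = 124.9, rounded up to 125 per arm. A noncentral *t* calculation gives 126 (power 0.8005), matching the stated 126.
- 126/(1 − 0.15) = 148.2, rounded up to 149, in line with the stated 150.

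**Step 4: what misreading could do (illustration on assumed values).** Assume the true three-parallel proportion is p₀ = 0.70 in both arms and that an assessor who recognises the arm upgrades a fraction u of the other navigated cases.
- Observed navigated proportion: p₁ = 0.70 + 0.30u
- Chance of a significant result favouring navigation: Φ[(p₁ − p₀ − 1.96·s₀)/s₁]
- s₀ = √[2p̄(1 − p̄)/n], with p̄ = (p₀ + p₁)/2
- s₁ = √{[p₀(1 − p₀) + p₁(1 − p₁)]/n}

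Worked case, u = 0.30 and n = 126: p₁ = 0.79, p̄ = 0.745, s₀ = 0.0549, s₁ = 0.0546. Then (0.09 − 1.96 × 0.0549)/0.0546 = −0.32, and Φ = 0.37.

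| u | p₁ | n = 126 per arm | n = 150 per arm |
|---|---|---|---|
| 0.10 | 0.73 | 8% | 8% |
| 0.20 | 0.76 | 19% | 21% |
| 0.30 | 0.79 | 37% | 43% |
| 0.40 | 0.82 | 61% | 68% |

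The reference value is 2.5%, the favourable half of the two-sided 5% level in Statistical Plan. The calculation treats the outcome as three-parallel or not and ignores site. The planned generalized mixed model would give somewhat different figures.

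**Step 5: first-pass success.** The Introduction cites it as a two-arm contrast (93.3% against 60%). The Results section plans it as a device-performance metric in the intervention group. As planned, it has no control-arm value.

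**The case against.** The strongest reply is that the protocol claims blinding for all imaging and that nothing shows the hardware in a scored view. The pins sit at the iliac spine and femoral condyle, and trimming them to keep images clear counts against visibility at least as much as for it. Nothing says assessors receive the full series. All of that stands, and it is why this is a risk and not a proven failure. It does not repair the mechanism: coding gives no protection if the hardware is visible, and no other safeguard is described.

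A reader might infer more than the documents support:

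- **That the trial has no unbiased between-arm look at placement.** Postoperative films and CT in both arms are reviewed for fixation position after the pins are out, and the assessor blinding covers them. What is missing is a named outcome from that review.
- **That the marker spheres unblind the reading.** They are documented for views taken before any wire is inserted.
- **That the operating team scores the outcome, because Table 2 ticks guide pin implantation in the Surgery column.** The column marks a time point. Neck-shaft angle is ticked there too, although it is defined on postoperative radiographs.
- **That wire passes go unrecorded in controls.** The protocol does not say so, and the case report form is not shown.
- **That the lack of an angle cut-off for parallel is an error.** A reading rule of that kind may sit in the full protocol or SAP.

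Making first-pass success a secondary outcome would not solve the problem either. It would be recorded during surgery, where the surgeon is unblinded. With enrolment running from June 2024 to October 2026, values for controls already operated on may not be recoverable.

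**Conclusion.** The point holds as a limited one. The only named between-arm placement outcome is read while navigation-only pins are in the patient, under a blinding method that would not conceal the arm if the pins or the image series reveal it. Visibility in the scored views is possible but not stated.

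The consequence cannot be fixed from the documents. Under the assumed 70% rate and a 10% to 40% upgrade of the remaining navigated cases, false significance in favour of navigation runs from about 8% to 61% at 126 per arm. If assessors cannot tell the arm, or can tell and do not shift their reading, there is no inflation from this source. First-pass success, as planned, describes the navigated arm and cannot carry a randomised claim. This concerns one secondary outcome. It is worth correcting because the correction is cheap.

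**What to change.** 1. In Secondary Outcomes and Table 1, define screw parallelism on the first scheduled postoperative anteroposterior and lateral radiographs, or add it as the blinded version of this outcome. The existing blinded radiographic assessors would score it. Keep the intraoperative wire reading as supportive.
2. Reconcile when the first film is taken. Table 2 ticks radiography at 2 weeks, while Follow-Up Visits lists radiographs from 1 month and only wound assessment at 2 weeks. The outcome definition should name the agreed visit.
3. State that first-pass success describes device performance in the intervention arm and will not be reported as a randomised comparison.

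**Cost.** Two definitions change. The radiographs are already scheduled in both arms, so no visit or exposure is added, and patients already operated on can be scored from stored films. As the article reports that no analysis has been performed, the change can be made and dated without knowledge of results. The main downside is that the outcome then describes screws, which follow the wires, and not the wires themselves. The primary outcome and sample size stay as they are.

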#### Safety Events

The safety end points mainly include the incidence of device-related adverse events, device deficiencies, adverse events, and serious adverse events. These outcomes will be evaluated over the entire follow-up period and are defined as follows:

Device-related adverse event: a problem caused by the test medical deviceDevice deficiency: any issue with the investigational device that could pose an unacceptable risk to patient health or safety during normal use, including deficiencies in labeling, manufacturing, malfunction, or performance failureAdverse event: any negative health change occurring in participants during this study, regardless of whether it is linked to the test deviceSerious adverse event: any adverse event resulting in death, a life-threatening situation, persistent, significant disability or incapacity, requiring hospitalization or extend existing hospitalization, or requiring medical or surgical intervention to prevent permanent damage

All outcomes measures are listed in Table 1.

**Table 1 table1:** Summary of all outcome measures.

Outcome categories and measures			Definition		Assessment time points
Primary outcomes: fluoroscopy frequency			Total number of intraoperative fluoroscopic images acquired during the procedure		Intraoperative period
**Secondary outcomes**					
	Neck-shaft angle	Angle between the femoral shaft axis and the femoral neck axis		Intraoperative period	
	Guide wire placement accuracy	Classification of guide wire arrangement as 3 parallel, 2 parallel, or nonparallel		Intraoperative period	
	Surgical duration	Time from skin incision to wound closure		Intraoperative period	
	Intraoperative blood loss	Total blood loss collected through suction		Intraoperative period	
	Fracture healing status	Fracture healing assessed by implant stability, disappearance of the fracture line, and absence of displacement		1, 3, 6, and 12 months	
	Zarit Caregiver Burden Score	Assessment of caregiver burden		1, 3, 6, and 12 months	
	Harris Hip Score	Assessment of hip function recovery		1, 3, 6, and 12 months	
	36-Item Short Form Health Survey Score	Assessment of health-related quality of life		1, 3, 6, and 12 months	
**Safety events**					
	Device-related adverse events	Adverse events directly related to the study device		All follow-ups	
	Serious adverse events	Events causing death, disability, or hospitalization		All follow-ups	
	Device defects	Malfunction or labeling error that may pose a health risk		Intraoperative and follow-up	
	General adverse events	Any unfavorable medical event regardless of causality		All follow-ups	

### Follow-Up Visits

During the postoperative follow-up period, patients will be evaluated through scheduled outpatient visits. Wound healing will be assessed at 2 weeks after surgery. Radiographic examinations will be performed at 1, 3, 6, and 12 months postoperatively, while computed tomography scans will be obtained at 6 and 12 months after surgery. These imaging studies are reviewed to determine the position of the internal fixation system and the status of fracture healing. Functional scoring of the affected limb and general health assessments will also be conducted during these visits. The complete follow-up schedule is presented in Table 2.

**Table 2 table2:** Study procedures and visiting schedule.

Study activities		Screening (day −7 to 0)	Surgery (day 0)	Postoperative follow-ups				
				2 weeks	1 month+2 weeks or −2 weeks	3 months+2 weeks or −2 weeks	6 months+2 weeks or −2 weeks	12 months+2 weeks or −2 weeks
**Enrollment and consent**								
	Informed consent	✓						
	Demographic information	✓						
	Vital signs	✓	✓	✓				
	Medical history	✓						
	Laboratory tests	✓						
	Garden classification	✓						
	Time from injury to surgery	✓	✓					
**Surgical details**								
	Intraoperative blood loss		✓					
	Duration of surgery		✓					
	Guide pin implantation effect		✓					
	Intraoperative fluoroscopy (3-pin)		✓					
	Intraoperative fluoroscopy (total)		✓					
	Neck-shaft angle		✓					
	Reduction quality (satisfaction)		✓					
	Garden alignment index		✓					
	Implant handling evaluation		✓					
	Surgery-related record		✓					
**Clinical and imaging assessments**								
	Radiography	✓		✓	✓	✓	✓	✓
	Computed tomography scan	✓		✓			✓	✓
	Harris Hip Score	✓		✓	✓	✓	✓	✓
	36-Item Short Form Health Survey quality-of-life score	✓		✓	✓	✓	✓	✓
	Zarit Caregiver Burden Scale	✓		✓	✓	✓	✓	✓
	Local physical examination	✓		✓	✓	✓	✓	✓
	Rejection reaction		✓	✓	✓	✓	✓	✓
	Fracture healing				✓	✓	✓	✓
	Weight-bearing status				✓	✓	✓	✓
	Femoral neck shortening			✓			✓	✓
	Wound healing assessment			✓	✓			
**Safety monitoring**								
	General adverse events	✓	✓	✓	✓	✓	✓	✓
	Serious adverse events	✓	✓	✓	✓	✓	✓	✓
	Device-related issues		✓					
	Concomitant medications or treatments	✓	✓	✓				

### Data Collection

From preoperative screening to the end of follow-up, all patient information will be collected using standardized case report forms. These data will be entered into the National Real-World Research Platform for Orthopedics, Sports Medicine, and Rehabilitation. To support quality assurance and follow-up tracking, user accounts on the platform will have differentiated access privileges. Data managers will review all entries in the case report forms. If any inconsistencies are identified, queries will be generated and sent to the investigator through the clinical research associate using standardized data query forms. The data manager will make database changes or confirmations based on the investigator’s feedback. If more details are needed, further queries may be issued.

